### Study schedule and assessments

The study flow and visit schedule are shown in **Table 2**. Baseline data, such as ECOG score, QLQ-C30 score, height, weight, physical examination, vital signs, laboratory examination, electrocardiogram, lung function, mMRC score, CAT score, ABCD grouping, and AECOPD severity, will be recorded during the screening period (less than 2 weeks prior to initial administration of the study drug). Previous and recent tumor samples will be collected. The expression of PD-L1 in tumor tissue samples will be determined via immunohistochemical staining, and the expression of CD4+ and CD8+ T lymphocytes will be determined via immunofluorescence staining.

**Table 2 T2:** Study flow chart and visit schedule.

FLOW CHART	Screening	Treatment visit	End of treatment visit	Safety follow-up visit
Timepoint	-d14–d0	Before dosing every cycle	Within 7 days after termination of treatment	Within 30 days after the last dose
Informed consent	X			
Inclusion and Exclusion criteria	X			
Demographic characteristics	X			
Medical history and treatment history	X			
Physical examination	X	X	X	X
ECOG score	X	X	X	X
QLQ-C30 score	X	X	X	X
Vital sign	X	X	X	X
Tumor tissue sample	X			
Virus detection:HbsAg,HbsAb,HbcAb,HCVAb,HIVAb	X			
Complete blood count, Urine Routine Examination	X	X	X	X
Alanine aminotransferase, Aspartate aminotransferase, Direct bilirubin, Total bilirubin, Glucose, Potassium,Sodium,Calcium, Phosphorus, blood urea nitrogen,Creatinine,Creatinine clearance, Total cholesterol	X	X	X	X
Activeated partial thromboplastin time, Prothrombin time, Thrombin time,International Normalized Ratio	X	X	X	X
Pregnacy test	X		X	
Free triiodothyronine, Free thyroxine, Thyroid-stimulating hormone	X	X	X	X
Cortisol, Adrenocorticotropic hormone	X	X	X	X
12-lead electrocardiogram	X	X	X	X
Echocardiography	X			
Lung function	X	Once every 3 months	X	
Evaluation of COPD symptoms	X	Once every 3 months	X	
Risk assessment of COPD exacerbations	X	Once every 3 months	X	
Evaluation of severity of acute exacerbation of COPD	X	Once every 3 months	X	
Drug administration		X		
Chest and abdominal CT (or abdominal and adrenal ultrasound), Cranial enhanced MRI,Neck ultrasound, Bone ECT, PET-CT	X	X		
Adverse events and drug combinations	X	X		
Survival follow-up		X		

Baseline tumor imaging evaluation will be completed within 2 weeks of initial treatment. Imaging evaluation will be performed every 6 weeks for 6 months from the first pembrolizumab dose and approximately every 12 weeks thereafter until disease progression or early withdrawal. The anti-tumor efficacy will be evaluated according to RECISTv1.1 and irRC (23).

Pembrolizumab-related AEs will be determined after each treatment cycle. The severity of AEs will be determined according to NCI-CTC AE 5.0. Investigators will be responsible for the appropriate measurement of AEs and will determine the relationships between AEs and the study drugs. AEs will be followed up until they were grades 0 to 1 or stabilized or returned to baseline levels. COPD status will be evaluated every 3 months according to pulmonary function, GOLD grading, mMRC score, CAT score, ABCD grouping, and AECOPD severity (24).

HRQoL will be assessed by completing the European Organisation for Research and Treatment of Cancer core quality of life questionnaire (QLQ-C30) at baseline, evaluation visits, end-of-treatment visits, and safety follow-up visits (within 30 d after the last dose).

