
### Patient withdrawal

Patients will be withdrawn from this study for the following reasons: (1) Subject or legal representative requests early withdrawal; (2) Unexpected rapid progression or radiographically confirmed disease progression occurs; (3) COPD-related exacerbations progress to acute exacerbation of chronic obstructive pulmonary disease (AECOPD) grade II-III; (4) Occurrence of any of the following during treatment: grade 3 hematologic toxicity, grade 3 neutrophil count decrease with fever (>38.5°C), grade 3 thrombocytopenia with bleeding tendency, esophageal perforation, severe pulmonary/mediastinal infection, hemorrhage, myocardial infarction, heart failure, severe arrhythmia, grade 2 or higher grade immune pneumonia, grade 3 or higher grade immune hepatitis, infusion reactions, or other immune-related toxicity; (5) 2-week treatment delay (for any reason); (6) Pregnancy; (7) The investigator considers it necessary to withdraw a patient from the study; (8) Subject cannot be followed up. All patients who withdraw will be followed up according to the study protocol, and the follow-up results will be recorded unless the patient withdraws informed consent and refuses to follow-up.

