### Outcome measurements

The primary outcome is PFS, defined as the time from randomization initiation to the progression of tumor or death for any reason (refer to RECIST v1.1).

The secondary outcomes include objective response rate (ORR), overall survival (OS), rate of acute COPD exacerbations (times/year), lung function, mMRC score, CAT score, impact of treatment on patient’s health-related quality of life (HRQoL), antibiotic use (including duration and classes), and AEs associated with immune checkpoint inhibitors. ORR is defined as the proportion of patients with complete response (CR) and partial response (PR) and is used to estimate the treatment efficacy according to RECIST v1.1. OS was measured as the period from the diagnosis of lung cancer to death. Acute exacerbation was defined if respiratory tract symptoms such as cough, sputum production, and dyspnea were significantly worse than usual, and the treatment program had to be adjusted, such as by using oral or intravenous glucocorticoid treatment combined with or without antibiotics, while excluding pneumothorax, heart failure, pneumonia, and other diseases. Acute exacerbations of COPD are classified as Grades I-III according to clinical symptoms.

Exploratory endpoint is to explore the association between COPD grade and the degree of immune cell (CD4+ T lymphocytes and CD8+ T lymphocytes) infiltration, as well as the association between COPD grade and the efficacy of immune checkpoint inhibitors.

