### Statistics

#### Determination of sample size

Based on the data from the KEYNOTE-042 study, the median PFS of the target subjects receiving the trial treatment in this study is expected to be 6 months. The enrollment time is 1.5 years, and the follow-up time is 1 year. The type I error rate is 5%, and the power is 80%. Considering a 10% abscission rate, the current study will include 30 patients with advanced NSCLC with COPD.

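### The imaging stop rule conflicts with the promised follow-up of withdrawn patients, so progression may go unobserved after COPD exacerbation, toxicity or treatment delay, and median PFS may be biased

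*Protocol article*

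**What the plan says.** **Primary outcome.** The Outcome measurements section defines PFS as running "to the progression of tumor or death for any reason (refer to RECIST v1.1"). Planned analyses specifies a Kaplan-Meier median with a 95% confidence interval.

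**Imaging.** Under Study schedule and assessments, scans are every 6 weeks for 6 months from the first dose and "approximately every 12 weeks thereafter until disease progression or early withdrawal". Table 2 marks imaging at screening and at treatment visits, with no entry at the end-of-treatment or safety follow-up visit.

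**Withdrawal.** The Patient withdrawal section opens with "Patients will be withdrawn from this study for the following reasons". The reasons include "COPD-related exacerbations progress to acute exacerbation of chronic obstructive pulmonary disease (AECOPD) grade II-III", a list of toxicities, and "2-week treatment delay (for any reason"). The same section then says "All patients who withdraw will be followed up according to the study protocol, and the follow-up results will be recorded", unless the patient withdraws consent and refuses follow-up.

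**COPD outcome.** A secondary outcome is the "rate of acute COPD exacerbations (times/year"). COPD status is assessed every 3 months. Table 2 has COPD entries up to the end-of-treatment visit and none at the safety visit.

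**Sample size.** Expected median PFS is 6 months, enrolment 1.5 years and follow-up 1 year. "Considering a 10% abscission rate, the current study will include 30 patients with advanced NSCLC with COPD".

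**The concern.** PFS by RECIST v1.1 needs scans to date progression. One section ends scans at early withdrawal, and another makes worsening COPD, toxicity and delay grounds for leaving the study. Read together, they end observation of the primary endpoint when the comorbidity under study, or the drug's toxicity, becomes serious. Patients in that position may well progress or die sooner than those who stay. If they are censored there, the Kaplan-Meier curve leans on the patients whose course was quieter.

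The promise of follow-up after withdrawal points the other way, but it refers back to the protocol, and the only imaging schedule shown ends at withdrawal. Two investigators could follow the same text and do different things. Scans that were not taken cannot be recovered at analysis.

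Two further quantities depend on the answer: how exacerbations after the first grade II-III event are counted, and whether a 10% attrition allowance is enough.

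**Working it through.** **Inputs from the protocol article (Determination of sample size):** median PFS 6 months, accrual 18 months, further follow-up 12 months, N = 30, attrition 10%.

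**Assumed, because the documents give no figure:** the rate of withdrawals that end PFS assessment, 0.17 to 1.0 per patient-year; the ratio k of the hazard after withdrawal to the hazard before, 1.5 to 3. Hazards are constant and accrual is uniform.

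**Step 1. The plan's own figure.** 27 / 0.9 = 30, so N = 30 fits 27 evaluable patients plus 10%. The 27 cannot be rederived, because no null median is stated.

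**Step 2. Events if imaging continues to progression or death.** With λ = ln 2 / 6 = 0.1155 per month,

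P(event) = 1 − (e^(−12λ) − e^(−30λ)) / (18λ) = 1 − (0.25 − 0.03125) / 2.079 = 0.895.

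Expected events are 30 × 0.895 = 26.8, or about 24 with 10% truly lost.

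**Step 3. Events if imaging stops at withdrawal.** Let w be the monthly withdrawal rate and t = λ + w, and let P(t) be the Step 2 formula with t in place of λ. The share withdrawn first is (w/t) × P(t). Observed PFS events are 30 × (λ/t) × P(t).

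| Rate per year | t | P(t) | Withdrawn first | PFS events of 30 |
|---|---|---|---|---|
| 0.17 | 0.1297 | 0.918 | 10.0% | 24.5 |
| 0.5 | 0.1572 | 0.950 | 25.2% | 20.9 |
| 1.0 | 0.1989 | 0.975 | 40.9% | 17.0 |

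The base is 30. Starting from 27 would take attrition off twice.

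**Step 4. Bias in the median.** Let the pre-withdrawal hazard be l. The true PFS curve, counting events after withdrawal, is

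S(t) = e^(−(l+w)t) + ∫₀ᵗ w e^(−(l+w)u) e^(−k·l·(t−u)) du.

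Solve S(6) = 0.5 for l. Kaplan-Meier with censoring at withdrawal then reports ln 2 / l.

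| Rate per year | k = 1 | k = 1.5 | k = 2 | k = 3 |
|---|---|---|---|---|
| 0.17 | 6.0 | 6.1 | 6.2 | 6.3 |
| 0.5 | 6.0 | 6.32 | 6.58 | 7.01 |
| 1.0 | 6.0 | 6.59 | 7.11 | 8.00 |

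Entries are reported medians in months when the truth is 6.0. If k is below 1 the bias reverses. Viewed the other way, at 1.0 per year with k = 0.5, a reported 6.0 months goes with a true median of 6.91.

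**Step 5. Exacerbation rate if counting stopped at the first grade II-III event.** Events divided by person-time are unbiased under a homogeneous Poisson process. If risk varies between patients (gamma-Poisson, dispersion 1, one year), a true 0.5 per year reads 0.41 and a true 1.0 reads 0.72.

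**The case against.** The strongest defence is that the phrase early withdrawal may be narrow. In the Patient withdrawal section it appears only in the first reason, a request by the subject or legal representative. Exacerbation, toxicity and delay are separate reasons. On that reading imaging continues after those events, in line with the follow-up promise. The reading is possible, but the same section withdraws every listed patient from the study, so the broad reading is equally open. That leaves a conflict to resolve on the primary endpoint.

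Table 2 is also weak evidence taken alone. It has no column beyond 30 days after the last dose, and it marks survival follow-up only under treatment visits although overall survival is a secondary outcome. Its blank cells may reflect condensation or lost formatting. The explicit stop rule in the text does not depend on them.

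A reader might go further in three ways that the article does not support:

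- **That PFS is informatively censored and biased upward.** No censoring rule is stated, and such rules are commonly left to the analysis plan. Direction and size depend on k, which is not given.
- **That the exacerbation rate is truncated at the first grade II-III event.** Nothing says so. The text sets no stop for the 3-monthly COPD evaluation, grade I events trigger no withdrawal, and Step 5 shows that a person-time rate can be unbiased even with such a stop.
- **That 10% attrition is not credible.** Withdrawal need not mean loss to analysis if follow-up continues. Entry also requires COPD stable for at least 2 weeks and excludes severely impaired pulmonary function, so low withdrawal rates cannot be ruled out.

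**Conclusion.** The point stands as a conflict between the imaging stop rule and the promised follow-up of withdrawn patients, with a possible bias in the primary endpoint. If the imaging rule is applied to all withdrawals and those patients are censored, a true 6.0-month median would read about 6.1 to 8.0 months. Observed PFS events would fall from about 27 to between 25 and 17 of 30. These ranges illustrate 0.17 to 1.0 withdrawals per patient-year and k of 1.5 to 3. Both are assumptions, and with k = 1 there is no bias, only fewer events.

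The 10% allowance is undefined. If withdrawal does end PFS assessment, 10% is enough only while all triggers combined stay at or below about 0.17 per patient-year. The article neither justifies nor contradicts such a rate. Off-treatment capture of exacerbations is left unclear, and no bias in that rate is established.

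**What to change.** Reconcile the Patient withdrawal section, the imaging text under Study schedule and assessments, and Table 2:

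1. Change the end of imaging to: until RECIST v1.1 progression, death or withdrawal of consent, regardless of treatment discontinuation.
2. Add off-treatment imaging and COPD/AECOPD follow-up to Table 2, as the withdrawal section already implies.
3. State that PFS is not censored at exacerbation, toxicity or treatment delay.
4. Report AECOPD as total events over total patient-years, including time off drug.
5. State what the 10% covers: loss of PFS assessment, or any withdrawal.

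The cost is a few lines of text and table entries, plus scheduled scans for patients off drug. Some of those patients will be on later therapy, so a PFS sensitivity analysis is needed. Recruitment is described as open, and scans missed meanwhile cannot be replaced, so the change is best made promptly. No change to the treatment-stopping or withdrawal criteria is proposed.

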### Data management

A paper case report form (CRF) will be developed before commencing the study. Patient information will be recorded using the CRF. The data manager will verify the CRF data, which will then be entered into a data management system. Doubtful data will be provided to the researchers for verification. Patient-identifying information, such as name, telephone number, and home address, will not be entered into the data management system. The verified data will be sent to statisticians for statistical analysis.

Some useful measures are often used to minimize the occurrence of lost follow-up. Firstly, a clinical nurse will be arranged to maintain long-term contact with the patien, and save information on commonly used contact methods of the patient such as telephone number, WeChat, email address, among others. In addition, the nurse will be in contact with the patient every other day to monitor the patient for immune-related adverse reactions. When the patient reports an adverse reaction, the nurse will promptly report it to the doctor, who will then contact the patient and give reasonable treatment. At the same time, it is also very important to save the contact information of at least one family member of the patient, so that the patient can be contacted in a timely manner.

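### Table 2 marks no adverse-event collection at the end-of-treatment or safety follow-up visit, and the text leaves open whether events are filtered by causality when recorded

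*Protocol article*

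**What the plan says.** Study schedule and assessments states that "Pembrolizumab-related AEs will be determined after each treatment cycle". The same paragraph adds that investigators "will determine the relationships between AEs and the study drugs", and that "AEs will be followed up until they were grades 0 to 1 or stabilized or returned to baseline levels".

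Table 2 in that section has four columns: screening, treatment visit (before dosing in every cycle), end-of-treatment visit (within 7 days of stopping) and safety follow-up visit ("Within 30 days after the last dose"). The row "Adverse events and drug combinations" is marked in the first two columns and blank in the last two. The row "Survival follow-up" carries one mark, under the treatment visit. No column lies beyond the safety follow-up visit.

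Two other sections bear on the point. Patient withdrawal says that "All patients who withdraw will be followed up according to the study protocol, and the follow-up results will be recorded", except where consent is withdrawn and follow-up refused. Data management says that "the nurse will be in contact with the patient every other day to monitor the patient for immune-related adverse reactions". Outcome measurements lists AEs associated with checkpoint inhibitors and OS as secondary outcomes, with OS running to death.

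**The concern.** Safety in patients with COPD is half of the trial's stated question. Two features of the text could make the safety result less complete than intended.

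- **Timing.** Treatment visits take place before dosing, so the last of them precedes the last dose. Events that arise after that dose would naturally be collected at the end-of-treatment and safety follow-up visits, and those are the two left unmarked. Patients who stop for toxicity or a pulmonary event go straight to these visits.
- **Causality.** If only drug-related events are determined, the investigator's attribution acts at collection and not at analysis. In a single-arm, unblinded COPD cohort, pneumonitis, infection and exacerbation can resemble one another. The exacerbation definition in Outcome measurements excludes pneumonia, so a pneumonia judged unrelated to the drug could count neither as an exacerbation nor as a related AE. It might then leave only indirect traces, such as antibiotic use.

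The survival row raises a lesser question: the table shows no contact after treatment for an endpoint that runs to death.

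**Working it through.** The plan states no figure on this point, so there is none to reproduce. The check is a reading of the passages side by side, followed by two illustrations of scale.

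**1. Table 2, row by row (as extracted)**

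| Row | Screening | Treatment visit | End of treatment | Safety follow-up |
|---|---|---|---|---|
| Physical examination, laboratory tests, ECG | X | X | X | X |
| Pregnancy test | X | blank | X | blank |
| Lung function | X | every 3 months | X | blank |
| AEs and drug combinations | X | X | blank | blank |
| Survival follow-up | blank | X | blank | blank |

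The extraction keeps blank cells in other rows, so a simple column shift in the AE row is unlikely. A merged cell cannot be excluded for either of the last two rows.

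**2. Table against text**

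- *Relatedness.* The quoted sentence names related events only. The Table 2 row carries no such limit, and judging the relationship of AEs to the drug presupposes that AEs are recorded first. The wording is ambiguous, not a clear restriction.
- *Time after the last dose.* Following an AE to grade 0–1, stabilisation or baseline applies to events already detected. The nurse contact has no stated end date, but it is aimed at immune-related reactions. Neither assigns AE collection to a visit after the last dose.
- *Survival.* The withdrawal section continues follow-up and OS runs to death, so the single mark under treatment visits conflicts with both.

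**3. Scale of the AE gap (illustration)**

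Assume a risk period of E weeks from first to last dose plus 30 days. The durations E are assumed; 26 weeks is about the expected median PFS of 6 months. Let u be the uncovered time after the last dose.

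Uncovered share = u / (E + 30/7), with 30/7 = 4.29 weeks.

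- Nothing captured after the last dose: u = 4.29 weeks.
- Last Q3W cycle captured, because AEs are determined after each cycle: u = 30 − 21 = 9 days = 1.29 weeks.

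| E (weeks) | Denominator | u = 4.29 | u = 1.29 |
|---|---|---|---|
| 26 | 30.29 | 14.2% | 4.2% |
| 12 | 16.29 | 26.3% | 7.9% |
| 6 | 10.29 | 41.7% | 12.5% |

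The share is largest for early stoppers under either reading. These are shares of time, not of events.

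**4. Why the survival row needs reconciling (illustration)**

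Assume exponential OS counted from enrolment, with median m between 16 and 30 months. The Introduction cites 20.0 and 30.0 months for pembrolizumab in other populations; 16 is an assumed lower value.

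- Alive at 6 months = 0.5^(6/m): 77% for m = 16, 81% for m = 20, 87% for m = 30.
- Take uniform accrual over a = 18 months and f = 12 months of further follow-up, from the sample size section, with λ = ln 2 / m. The proportion dead by cut-off is 1 − [exp(−λf) − exp(−λ(a+f))]/(λa). For m = 20 this is 1 − (0.660 − 0.354)/0.624 = 0.51, or about 15 of 30 patients. Over m = 16 to 30 the count is about 18 to 11.

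Most patients would therefore be alive at the expected median PFS, and the schedule should show how they are followed after treatment.

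**The case against.** The strongest reply is that the rest of the document supplies what the table leaves blank. Withdrawal triggers include specific toxicities, which must be identified and graded for the rule to operate. AEs are followed to resolution with no limit at the end of treatment. Safety tests are marked at both final visits. A nurse contacts patients every other day. AEs determined after each cycle would reach about 21 days past the last dose. Exacerbation rate, lung function, mMRC, CAT and antibiotic use are separate outcomes that do not depend on a drug-causality call. A survival row marked only before dosing makes little sense as a plan and looks like a merged cell.

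Much of this stands. It rules out three stronger readings that a reader might infer.

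- *AE collection is restricted to related events.* The table row and the causality sentence point the other way.
- *14% to 42% of the risk period is lost.* Those figures require no capture at all after the last dose. Counting the last cycle reduces them to about 4% to 13%, and nurse contact may reduce them further.
- *OS is cut short.* Follow-up after withdrawal is stated, OS is defined to death, a nurse and a family contact maintain long-term contact, and one year of follow-up is planned.

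What the reply does not do is assign detection of new AEs to a visit after the last dose, or settle whether unrelated events are recorded. Follow-up after withdrawal is itself to be done according to the study protocol, and the schedule shown has no column after the safety visit. Fixing the safety visit on an exact day, or prescribing side-by-side AE tables, would be a matter of convention or of the analysis plan and is not part of this point.

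**Conclusion.** The point holds as an inconsistency in a stated schedule together with an ambiguous sentence. As extracted, Table 2 assigns no AE collection to either visit after the last dose, including the one named for safety, and the text permits events to be filtered by an unblinded causality judgement at collection. The survival row should be reconciled with the withdrawal section and the OS definition.

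The size of the loss is not established. The illustrative range of about 4% to 42% of the risk period rests on an assumed 30-day window, on assumed durations of 6 to 26 weeks, and on whether the last cycle is covered. It is not an estimate of missed events. The finding also rests on the extracted table being faithful. It shows neither that safety data will be truncated nor that deaths after treatment will go uncounted. It is a minor to moderate defect, worth correcting because correction costs almost nothing.

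**What to change.** 1. In Table 2, mark AE and concomitant-drug collection at the end-of-treatment visit and at the safety follow-up visit.
2. In Study schedule and assessments, reword the AE sentence so that all AEs, whatever their cause, are recorded from the first dose through the safety follow-up visit, with the investigator's relatedness judgement kept as an attribute of each event.
3. In Table 2, show survival follow-up after treatment, so that the schedule agrees with the Patient withdrawal section and the OS definition. If the present mark is a merged cell, correct the layout.

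The cost is a change to one table and one sentence. Both visits already exist and nurse contact is already planned, so the burden is a little more recording. Reported AE rates may rise slightly because unrelated and late events will be counted; the related subset can still be reported for the stated endpoint.
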